To test the HAPA tenets in middle-aged postmenopausal women while filling the abovementioned gaps in the literature, the main aim of this study is two-fold. First, we aim to explore the influence of the social-cognitive variables relevant at each stage of the process of behavioural change based on HAPA predictions, and second, to test the goodness of fit of the model for exercise behaviour among women in early postmenopause (up to ten years after menopause). Specifically, the sub-aims of the present study protocol are the following:To explore the HAPA constructs at every stage of the change process in new exercisers, that is participants adhering to exercise practice while simultaneously receiving an intervention based on the HAPA model (Intervention group). These will be compared with regularly active (active control) and non-active (sedentary control) postmenopausal women, all with different socio-demographic, personal and clinical characteristics. Consequently, this sub-aim has the following specific objectives:to determine changes in the HAPA variables in the intervention group throughout the study phases, and in this regard:H1: we hypothesise that there will be a significant improvement in both intentional-motivational and postintentional-volitional variables in the participants in the exercise programme supplemented with the HAPA intervention.to compare the intervention, sedentary and active groups across the motivational and volitional phases of the HAPA model, and in this regard:H2: we hypothesise that, at baseline, non-active women (i.e., sedentary and intervention groups) will show similar HAPA determinants of exercise intention, while the active controls will obtain more positive results in the HAPA motivational constructs, andH3: we hypothesise that, at post-intervention and subsequent follow-ups, the new exercisers and the active women will show similar HAPA self-regulatory skills of the volitional-actional stage but will differ significantly from the sedentary women.To explore whether the HAPA constructs at the different stages of the process of behavioural change — i.e., non-intention, intention, action and disengagement — and phases of the process, that is, motivational (preintention) and volitional (intention-action-adherence), predict the adoption of exercise behaviour among postmenopausal women. In this regard:H4: we hypothesise that while the HAPA model will be applicable to this population, supporting its main predictions, adjustments in the model predictions will be necessary to optimise its explanatory power, considering the experiences, resources and opportunities of middle-aged women, andH5: personal (i.e., fitness status, physical and mental health status and sociodemographic variables) and clinical factors (i.e., menopausal manifestations and menopause-related quality of life) will intersect with HAPA variables in the prediction of exercise behaviour and behaviour change, supporting the existence of phenomena that are pertinent and exclusive of middle-aged women and are grounded in their experiences, realities and needs.

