After enrolment, participants will be assigned to one of three study groups by randomisation and non-randomisation, depending on the study condition. The groups are as follows: 1) Intervention-initiators (participants who will engage in a supervised exercise programme complemented with a HAPA-based intervention, *n* = 100); 2) control-sedentary (non-active women who will maintain their sedentary lifestyle and will not receive any intervention for promoting behavioural change, *n* = 100) and 3) control-active (women with a regular and sustained exercise habit, *n* = 100).

The sample size has been calculated to include 80 participants per group, considering an *alpha* error of 0.05 and a *beta* error of 0.2, for independent groups and continuous variables, i.e. mean comparisons, with estimated mean values based on previously published studies [64, 65, 68], to ensure sufficient statistical power to detect a moderate treatment effect in a clinical study (Clincalc®). To account for potential dropouts, we anticipate a 20% dropout rate, increasing the sample size up to 100 participants per group. 

Figure 1 shows a flow chart of the study participants, including the selection process.

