To address the first research question, exercise behaviour and HAPA constructs of the motivational and volitional phases (primary outcomes) will be compared across different phases (baseline, post-intervention and follow-ups) (H1) and between the different study groups (intervention participants, sedentary controls, active controls) (H2 and H3). Within-group and between-group analyses will be conducted using parametric (e.g., 1-way or 2-way ANOVAs, Student *t* test) or non-parametric tests (e.g., Friedman’s *χ*^*2*^ test and Wilcoxon’s *Z* pair comparisons for related samples, Kruskal–Wallis’ *H* test and Mann–Whitney’s *U* pair comparisons for independent samples). The choice of test will be determined by the compliance with parametric assumptions of normality and homoscedasticity. A calculation of the effect size will be also conducted (e.g., Cohen’s d). Covariates (e.g., age, menopausal symptom burden) will be introduced (e.g., ANCOVAs).

The second research question (H4 and H5) will be addressed using analyses of bivariate associations (e.g., Pearson *r*, Spearman *rho*), multiple linear regression analyses and multilevel clustering analyses to explore the correlates and predictors of outcome variables as well as intraindividual profiles or patterns of associations. Path analyses and analyses of indirect relationships between variables (e.g., mediation, moderation) will allow for a deep understanding of the complex associations between the study variables. Structural equation modelling will allow for testing the fit of data to the model based on HAPA predictions. Covariates will be introduced to control for their confounding effects (e.g., perceived health status). 

In addition, psychometric properties of the measures will be analysed (e.g., Cronbach’s *alpha*, intercorrelations).

A significance level of *p* < 0.05 will be established.

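### Half of H3 predicts that intervention and active women will be similar, but the tests assigned to H3 can only refute similarity, not support it

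*Protocol article*

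**What the plan says.** In the protocol article, the section on aims and hypotheses gives H3 two halves, both applying at post-intervention and the later follow-ups. The first is that "the new exercisers and the active women will show similar HAPA self-regulatory skills of the volitional-actional stage". The second is that these women "but will differ significantly from the sedentary women".

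Data management and analyses handles H3 by name. Exercise behaviour and the HAPA constructs, which it calls primary outcomes, are to be compared "between the different study groups (intervention participants, sedentary controls, active controls) (H2 and H3"). On the method it says: "Within-group and between-group analyses will be conducted using parametric (e.g., 1-way or 2-way ANOVAs, Student *t* test) or non-parametric tests". It adds: "A calculation of the effect size will be also conducted (e.g., Cohen’s d"). On the decision level it says: "A significance level of *p* < 0.05 will be established".

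Participants and eligibility criteria bases the sample size on "an *alpha* error of 0.05 and a *beta* error of 0.2, for independent groups and continuous variables, i.e. mean comparisons", "to ensure sufficient statistical power to detect a moderate treatment effect in a clinical study". This gives 80 per group, raised to 100 for 20% dropout.

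The article gives no margin, interval rule or other criterion for calling two groups similar.

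**The concern.** The two halves of H3 need different kinds of evidence. The named tests all take no difference as the null hypothesis. That suits the half on differing from sedentary women. For the half on resembling active women, the predicted state is itself the null. A small p-value counts against the prediction, and a large one shows only that the data did not rule it out.

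The claim at stake is substantive. Active controls are not randomised and must have exercised regularly for at least 12 months, so nothing in the design makes the intervention women like them. Saying that the two groups are alike means that a programme of three months or more brought sedentary women to the self-regulatory level of habitual exercisers. If that rested on non-significance, a shortfall as large as the trial was built to detect could pass as similarity, and more readily as data are lost.

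The similarity that H2 predicts at baseline between the intervention and sedentary groups is a different case. Those groups are randomised, so likeness is expected by design.

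**Working it through.** **Inputs from the article.** Alpha 0.05, beta 0.2, 80 per group before dropout, 20% dropout, 100 per group recruited.

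**Assumptions.** Two-sided tests (sidedness is not stated), equal group sizes, SD = 1, one construct at one visit. The case of 50 per group is a pessimistic assumption and not a planned figure.

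**1. The plan's own figures.** Dropout: 80 / (1 − 0.20) = 100, which agrees. The 80 cannot be checked because no means or SD are given. By the normal approximation, the effect that 80 per group detects with 80% power is (1.960 + 0.842) × √(2/80) = 2.802 × 0.158 = 0.443 SD. With the noncentral t it is 0.446 SD. This fits a loose reading of a moderate effect, so the 80 is not shown to be wrong. I use 0.45 SD as a round value.

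**2. Chance that a true deficit of 0.45 SD gives p ≥ 0.05.** The noncentrality is d × √(n/2), and power comes from the noncentral t with 2n − 2 degrees of freedom.

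| n per group | noncentrality | power | P(non-significant) |
|---|---|---|---|
| 80 | 0.45 × √40 = 2.846 | 0.808 | 19% |
| 50 | 0.45 × √25 = 2.250 | 0.606 | 39% |

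If the groups are truly equal, the chance is 95% at any n. Losing data therefore makes the similarity half easier to support when a real difference exists.

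**3. H3 as a whole.** I simulated all three pairwise t tests (200,000 runs, SD 1). H3 counts as supported when intervention versus active is non-significant and both groups score significantly higher than sedentary. The effects are assumed.

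| Intervention over sedentary | Intervention below active | 80 per group | 50 per group |
|---|---|---|---|
| 0.45 SD | 0 | 68% | 44% |
| 0.45 SD | 0.30 SD | 48% | 48% |
| 0.30 SD | 0.30 SD | 33% | 26% |
| 0.45 SD | 0.45 SD | 18% | 31% |

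Attrition raises support for the whole hypothesis in one of the four scenarios. In the others support falls or is flat, because the half on differing from sedentary women becomes harder.

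**4. What an equivalence rule would do.** Use two one-sided 5% tests, that is, require the 90% CI to lie inside ±m. If the groups are truly equal, power ≈ 2Φ(m/SE − 1.645) − 1, with SE = √(2/n).

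- m = 0.45, n = 80: SE = 0.158 and m/SE = 2.846, so 2Φ(1.201) − 1 = 0.770. With the t critical value it is 0.767, about 77%.
- m = 0.45, n = 50: m/SE = 2.250, so 2Φ(0.605) − 1 = 0.455. With the t critical value it is 0.444, about 44%.
- False acceptance when the true deficit equals the margin: about 5% at both sizes.
- With 80 per group, power is 87% at m = 0.5, 62% at m = 0.4 and 20% at m = 0.3.

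Under this rule, losing data lowers the chance of claiming similarity.

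**The case against.** The strongest reply is that the misuse is inferred. A reader might conclude that the plan will treat non-significance as proof of similarity, but the article nowhere says so. Its test lists are given as examples, an effect size is planned, and a rule could sit in a fuller plan. The first part of this stands. What remains is that the article names the hypothesis, the test family, the alpha level and the basis for power, and these together cannot support half of that hypothesis. A point value of d without an interval or threshold does not change this. A margin set elsewhere would need a different test from those named here.

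A reader might also infer that the more women are lost, the more often H3 is confirmed. The documents do not support that. H3 joins two predictions, and step 3 of the working shows that attrition usually lowers or leaves unchanged the support for both together.

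It is tempting to lead with a 0.3 SD deficit, which is missed 53% of the time with 80 per group. Under a 0.45 SD margin, however, such a deficit would count as similar, so it is not a clear error by that standard.

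The case of 50 per group is not forecast either. The Discussion's remark that up to half of participants do not take up the habit concerns exercise, not missed assessments. Non-adherent women stay in the analyses, and carrying the last observation forward could hold up numbers among controls.

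Finally, the error rates are per construct and visit. If similarity were required on every construct and visit, false support would be rarer.

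**Conclusion.** The point holds for the intervention-versus-active half of H3 only. The methods named for it can contradict similarity but cannot establish it. The size is about a 19% chance, per construct and visit, that a true 0.45 SD deficit goes undetected with the planned 80 completers per group, and 39% with an assumed 50. These figures rest on two-sided tests, equal groups and a standardised effect back-calculated from the 80, because the article states no means or SD.

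H1, the randomised comparison with sedentary women and the difference half of H3 are unaffected. The matter should be fixed, but it is not critical: it concerns how one half-hypothesis is judged, and it can be put right without new data.

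**What to change.** For the intervention-versus-active half of H3, state that the difference will be reported with its 95% CI for each volitional construct and visit, and that similarity will not be inferred from p > 0.05. Allow a claim of similarity only if the 90% CI lies wholly inside a margin that is justified on substantive grounds and fixed before data are seen. A margin of 0.45 SD illustrates the rule, but it comes from the sample size and is not a substantive threshold. If no margin can be agreed, make this half of H3 descriptive. Keep difference tests for the comparisons with sedentary women.

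This costs a few lines of analysis text and the work of justifying a margin. Similarity becomes harder to claim, and the trial was not sized for it. Even truly equal groups would miss a 0.45 SD margin about 23% of the time (100% − 77%) per construct and visit with 80 per group, and a tighter margin would be missed more often.

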The HAPA model has been tested with a wide range of populations, sociocultural backgrounds and health behaviours, and has demonstrated its universality and stability across different scenarios [37, 43, 54]. Nevertheless, the existing evidence also points to certain differences based on gender, age, type of behaviour or health status. While the model is applicable to all individuals, some findings indicate that certain adjustments could enhance its applicability and power. For instance, some evidence indicates that the HAPA model is particularly applicable to middle-aged and older adults in predicting an active lifestyle [55] and interventions tailored to specific age groups [56] are expected to be more successful than one-size-fits-all approaches. Other research indicates that adult women utilise different resources throughout the change process compared to men (e.g., higher planning, lower social support) [57–59], which could indicate that women face specific circumstances that make it more challenging to adopt a new habit and receive acceptance from their social contexts. As a result, they may be more likely to engage in less physical activity and require tailored interventions that are adapted to their particular realities, experiences, resources and opportunities. While initial meta-analytic research found minimal effects of age, gender or sample type as moderators of the associations between HAPA constructs and exercise behaviour [46], the findings also revealed high heterogeneity. More recently Choi et al. [48] reported that effect sizes for the predictions based on the HAPA tenets were larger in the healthy participants compared to patients, men compared to women and younger individuals compared to older ones. These findings are congruent with the notion that healthy people, men and younger individuals are more likely to engage in physical activity. Zhang et al. [43] concluded that the population characteristics that were found to have minimal differences did not deviate significantly from the tenets of the HAPA model. However, these findings stress the relevance of understanding the resources, opportunities and barriers involved in self-management and self-regulatory processes that some populations — such as middle-aged women who have gone through the menopause — may encounter when attempting to make behavioural changes. The authors thus recommended that interventions be tailored to the specific circumstances of the targeted individuals. All these findings stress the relevance of investigating the gender-, age- and health status-based specificity of the process of behavioural change for health-related actions and the associated factors and dynamics involved, which can inform the development of appropriate interventions [60].

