### Participants and eligibility criteria

The participants will be 300 postmenopausal women aged 45 to 65 years living in Granada, a city in the South of Spain with a population of > 230,000, as of 2023 [73]. Participants will be recruited using non-probabilistic, convenience procedures (see Procedure section).

Inclusion criteria will be: 1) being postmenopausal women between 45 and 65 years old; 2) with no menses for 12 months or more and up to 10 years after menopause, i.e., early postmenopause based on Stages of Reproductive Ageing Workshop STRAW + 10 criteria [74]; 3) able to speak and read Spanish with proficiency; and 4) able to provide informed consent for voluntary participation. Additionally, inclusion criteria for the intervention/sedentary control groups are: a) being sedentary (having not engaged in moderate-to-vigorous exercise on a regular basis, independent of daily physical activity, e.g., walking for transportation) for at least the 12 months prior to the beginning of the study, as screened with the self-report described below; b) able to exercise, i.e., in good health that allows them to exercise, based on medical criteria (see below); and c) willingness to be randomised to intervention/non-intervention (waiting list) conditions. For the active control group, these criteria are: i) exercising on a regular basis reaching international recommended levels for health promotion for at least the last 12 months, as screened with the self-report described below. In addition, exclusion criteria are: 1) use of hormone therapy in the three months before recruitment; and 2) suffering from any physical or mental disease that would seriously deteriorate functioning, impede participation in exercise based on medical criteria or introduce bias in responses. For the active participants, an athlete (i.e., competitive sport) of any performance level will be excluded. Selection criteria will be examined after recruitment to check eligibility and proceed with the study group assignment.

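### H5 concludes that phenomena are exclusive to middle-aged women, but only early postmenopausal women are studied, so no result can support or refute exclusivity

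*Protocol article*

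**What the plan says.** H5 is the last of five formal hypotheses in the protocol article (section on aims and hypotheses). It names two sets of factors:

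- Personal: "personal (i.e., fitness status, physical and mental health status and sociodemographic variables".
- Clinical: "clinical factors (i.e., menopausal manifestations and menopause-related quality of life".

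It predicts that these "will intersect with HAPA variables in the prediction of exercise behaviour and behaviour change", and it gives the meaning of that result in advance: "supporting the existence of phenomena that are pertinent and exclusive of middle-aged women".

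The section on participants and eligibility criteria fixes who is studied: "The participants will be 300 postmenopausal women aged 45 to 65 years living in Granada". The first inclusion criterion, common to all groups, is "being postmenopausal women between 45 and 65 years old". The second limits entry to at most ten years after menopause. The intervention, sedentary and active groups differ by activity status and by receipt of the intervention.

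The section on data management and analyses assigns the methods: "The second research question (H4 and H5) will be addressed using analyses of bivariate associations". It goes on to multiple regression, clustering, path models, mediation and moderation, and structural equation modelling.

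**The concern.** H5 joins two statements of different kinds. The first, that personal and clinical factors interplay with HAPA variables in predicting exercise, can be examined in this sample. The second, that the resulting phenomena are exclusive to middle-aged women, concerns everyone outside the sample as well. It needs evidence that the pattern is missing or different in men, in younger or older women, or in premenopausal women. None of these people are enrolled.

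The wording of one conclusion is at stake. If H5 is reported as written, an ordinary moderation effect could be published as a phenomenon specific to middle-aged women, and the data could neither confirm nor contradict that. The label is also wider than the sample: the women enrolled are in early postmenopause, which is only part of middle age.

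**Working it through.** No figure is stated for H5, so there is none to reproduce. The check asks whether the H5 result could come out differently if the phenomenon were exclusive than if it were general.

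**Step 1. What exclusivity requires.** Let b be the interplay (for example, an interaction coefficient) between a factor and a HAPA variable in the sampled women, and b* the same quantity in another population. *Exclusive* means b ≠ 0 and b* = 0. *General* means b ≠ 0 and b* = b. The two differ only in b*.

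**Step 2. What the data contain.** Every participant meets the common criterion of being postmenopausal and aged 45 to 65. The three groups contrast activity status and intervention, not sex, age band or menopausal status. The analyses assigned to H5 are all within-sample. The article plans no external data set and no comparison with published coefficients. Nothing in the data depends on b*.

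**Step 3. Consequence.**

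P(H5 supported | exclusive) = P(H5 supported | general), because both depend on b and n alone.

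Likelihood ratio = P(supported | exclusive) / P(supported | general) = 1, for any b and any n.

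**Step 4. Illustration.** Assume a standardised interaction b, residual SD 1 and a two-sided test at 0.05. The article gives no value for b, so two are shown. Sample sizes are 3 × 80 = 240 analysed after dropout and 3 × 100 = 300 enrolled. Approximate power is Φ(b√n − 1.96).

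| b | n | b√n − 1.96 | P(supported) if b* = 0 | P(supported) if b* = b |
|---|---|---|---|---|
| 0.1 | 240 | 1.549 − 1.960 = −0.411 | 0.34 | 0.34 |
| 0.1 | 300 | 1.732 − 1.960 = −0.228 | 0.41 | 0.41 |
| 0.2 | 240 | 3.098 − 1.960 = 1.138 | 0.87 | 0.87 |
| 0.2 | 300 | 3.464 − 1.960 = 1.504 | 0.93 | 0.93 |

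For b = 0.2, simulation of the regression (10,000 replicates, four runs per sample size) gave about 0.85 at n = 240 and about 0.92 at n = 300, slightly below the approximation. The level of power does not matter here. The last two columns are identical in every row, so a larger trial would detect the interplay more often and still say nothing about exclusivity.

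**Step 5. The two sets of factors.** Fitness, physical and mental health and sociodemographic variables exist in every population, so b* is well defined and Step 3 applies directly. Menopausal manifestations and menopause-related quality of life have no direct counterpart in men or premenopausal women, so for them b* is not well defined. What remains open is whether an effect of menopausal symptom burden differs from an effect of symptom burden in general. That too needs data from outside this sample.

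**The case against.** The strongest defence is that the menopausal factors are specific to this population by nature, so calling their interplay exclusive is close to a definition. That stands for the variables themselves and takes them out of the strict likelihood-ratio argument. It does not rescue H5: the same sentence attaches the conclusion to the personal factors, and a specific variable is not yet a specific effect.

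A second defence is that H5 is a hypothesis with an interpretive clause, placed under an exploratory sub-aim, and that the central objective is the applicability of HAPA within this population. Tailoring an intervention to these women needs evidence about them, not proof of absence elsewhere. This is fair and limits the consequence. It also shows that the project can do without the claim.

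Three stronger readings are tempting, and the article does not support them.

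- A reader might infer that one significant interaction among many, each at p < 0.05, is enough to confirm H5, and compute an inflated false-positive rate. The article states no such rule. The number of terms and the handling of multiplicity are commonly left to an analysis plan, which is not shown. Any such rate would rest on assumed correlations and would not bear on exclusivity.
- A reader might infer that the background already proves such interplay to be general, since it reports that "effect sizes for the predictions based on the HAPA tenets were larger in the healthy participants compared to patients". The same section also describes earlier meta-analytic work with minimal moderator effects but high heterogeneity, and another meta-analysis with minimal population differences. Contrasts between healthy and patient samples are also not interactions within one sample that excludes serious disease. The background leaves general moderation possible and does not establish it.
- A reader might infer that the other hypotheses, the randomised comparison or the sample size are undermined. None of them depends on this clause.

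**Conclusion.** The point holds as a defect in a stated inference. H5 announces support for exclusivity from a design with no comparison population and no external estimates, and so can neither support nor refute it. For the personal factors the result carries no information on exclusivity (likelihood ratio 1), whatever the effect or sample size. For the menopausal factors the variables are population-specific by definition, but a difference from a general symptom-burden effect cannot be shown.

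This rests on the eligibility criteria and on the analyses listed in the article. The effect sizes in the illustration are assumptions, and the conclusion does not depend on them. An analysis plan confined to this sample could not change the conclusion, because the missing element is data or estimates from other populations. The size is limited to one conclusion in one of five hypotheses.

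**What to change.** In H5, delete the words that claim exclusivity (*and exclusive*). Restate the hypothesis along these lines: personal and clinical factors moderate, or add to, the associations between HAPA variables and exercise behaviour within early postmenopausal women. Limit the conclusion to phenomena that are pertinent to this population, and name it as early postmenopausal women rather than middle-aged women in general. Both sets of factors stay in the hypothesis, and the planned analyses stay as they are.

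If the investigators wish to keep a claim of exclusivity, they would need a comparison population or a prespecified comparison with external estimates for the same associations.

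The rewording needs no new data, procedure or analysis. Its only cost is a narrower claim, and what is given up is something this design could not establish.
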